### Machine Learning

Machine learning techniques can reveal associations between variables, which are difficult to discover through statistical analyses [18]. Given the large volume of active ingredients to be analyzed and the high number of cases included in the database, in this study, as an additional step to the statistical analyses described below, machine learning techniques will be used to identify associations between the consumption of drugs and survival. The associations identified by machine learning techniques will later be confirmed by the classical statistical analyses described below.

Association rule mining (ARM), widely used for medical data analysis, will be used [19-21]. Through this method, association rules (ARs) are constructed that represent possible relationships between different elements within large data sets, identifying the most relevant ones. ARs consist of an antecedent (left hand side), which can be made up of several elements (drugs, age, etc), and a consequent (right hand side), which is made up of a single element, in the case of this study, survival at 5 years. In this study, a total of 2 sets of different ARs will be built using two approaches: (1) based on the amount of drug consumed, and (2) based on the time of drug consumption.

All variables will be previously categorized for use by the ARM technique. The survival variable will be treated dichotomously, depending on whether the patient has survived for at least 5 years. To obtain the set of rules based on the time of consumption of the drugs (active principles [ATC4] and families [ATC5]), the information will be categorically organized by quarters: whether the drug has been consumed during the quarter or not. To construct the set of rules related to the doses of drug consumed, the average DDD, discretized in 3 quantiles, will be used during the survival time of the patient.

Among all the rules generated by this methodology, the relevant ones will be selected. For this, an a priori algorithm [22] will be used to extract element frequencies, as it has been shown to be effective and is widely used in the literature [23].

Of all the rules produced using this methodology, only those that are met in at least 5 patients will be taken into consideration, and the most relevant will be selected using the following set of metrics:

Support is a measure that indicates the frequency of the combination of the antecedent and consequent in the data set.Confidence is a measure that indicates the probability of obtaining a consequent given an antecedent.Lift is a measure that indicates how much more the combination of the antecedent and consequent occurs compared with what would be expected if they were statistically independent.Conviction is a measure that evaluates the relationship between the antecedent and the consequent of a rule [24]. This measure takes into account the occurrence of both independently. It is defined as the ratio of the expected frequency of incorrect predictions made by the rule to the actual frequency of incorrect predictions made by the rule. As a general rule, those values that are further from 1 usually indicate the most interesting rules.

First, the data are preprocessed to obtain a column for each active substance in each patient and, depending on the desired screening, the amount of the active substance taken in the different quarters. Other relevant data, such as age and sex, are also added.

Subsequently, AR search algorithms are run on the processed data, with a support threshold set to avoid generating nonrelevant rules, for example, less than 5 patients. However, this support can be filtered again later. Obtaining ARs that indicate static relationships between the different attributes, filtering now those that present survival.

Finally, the filtered rules are sorted by the desired metric (eg, lift). This metric was chosen especially for its ability to find active ingredients with a higher-than-expected survival rate. In the example shown in Table 1, active substance 3 in a medium dose leads to 6 times longer survival than expected in these patients.

**Table 1 table1:** Example of the use of the association rule mining method for the analysis of survival associated with different active ingredients and combinations of active ingredients.

Antecedent			Quantity	Consequents		Support	n		Confidence		Lift	Conviction

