### Methods to Address Potential Sources of Bias

This study, given its retrospective nature, is potentially affected by a series of biases, whose prevention or compensation will be attempted through various techniques. The 3 most important biases are discussed below:

Reverse causality bias: drugs that are prescribed to patients near death to control their symptoms will appear associated with an increased risk of death in the analyses, with the prescription of these drugs not being the cause of death but a consequence of proximity to death. This bias will be alleviated by eliminating the drugs prescribed 3 months before death from the analysis.“Immortal patient” bias: the longer a patient survives, the more likely he or she is to be diagnosed with pathologies and to consume drugs. This can give the false appearance that the drugs consumed throughout life are the cause of prolonged survival. To control this effect, the analyses only considered the drugs consumed up to a certain date in the group of patients who survived until that same date. For example, in the group of patients who have survived at least 3 months after the diagnosis of their cancer, only drugs consumed at any time up to month 3 after the cancer diagnosis will be considered. Thus, the consumption of the drug will not be explained by longer survival because the entire group will have survived until the moment when the drugs under study are consumed. Patients who consume the study drugs after the established time cutoff point will be eliminated from the analysis. As a comparison group, only patients who have not consumed the drug at any point in their disease evolution will be taken into account.Diagnostic anticipation or “medical surveillance” bias: this bias occurs when patients are included in studies who are in a screening program for cancer because, in such programs, the cancer is diagnosed earlier, which causes the erroneous impression that the individuals live longer. In our database, patients with certain diseases may have undergone frequent diagnostic tests, thus triggering early cancer detection. For example, patients with chronic obstructive pulmonary disease (COPD) may have undergone periodic radiographs, in which lung cancer has been detected early. This may give the impression that COPD, or the drugs used by patients with COPD, are associated with increased survival from lung cancer. To control this bias, patients with a previous pathology that produces greater medical surveillance of the organ where the cancer developed will be eliminated from the analysis.

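### The association rules count drug use over each patient's own survival time, which conflicts with the protocol's landmark safeguard and inflates lift for inert drugs started after diagnosis

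*Protocol article*

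**What the plan says.** The Machine Learning section of the protocol article builds two sets of association rules.

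- **Outcome:** "The survival variable will be treated dichotomously, depending on whether the patient has survived for at least 5 years".
- **Time rules:** "the information will be categorically organized by quarters: whether the drug has been consumed during the quarter or not". No last quarter is named, and patients need not be alive at a common date.
- **Dose rules:** "the average DDD, discretized in 3 quantiles, will be used during the survival time of the patient".
- **Ranking:** four metrics are listed (support, confidence, lift, conviction). Filtered rules are sorted by a chosen one, with lift as the example. The reason given is: "This metric was chosen especially for its ability to find active ingredients with a higher-than-expected survival rate".
- **Reading of Table 1:** "active substance 3 in a medium dose leads to 6 times longer survival than expected in these patients".

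The section Methods to Address Potential Sources of Bias recognises that longer survival gives more opportunity to take drugs. Its remedy is that "the analyses only considered the drugs consumed up to a certain date in the group of patients who survived until that same date". According to the Results section, machine-learning analyses have already begun.

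**The concern.** A drug started after diagnosis can be recorded only while the patient is alive. If use is counted over the whole survival time and the outcome is being alive at 5 years, survivors have had longer to become users. Lift then exceeds 1 even when the drug does nothing.

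The dose rule adds a second distortion, because its denominator is the patient's own survival. Take an assumed single course of 90 DDDs. It averages 90/60 = 1.5 per month in a 60-month survivor and 90/6 = 15 per month in a patient who dies at 6 months. The same course falls into different dose thirds because of the outcome.

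The landmark rule would remove both problems, but an average over each patient's own survival time cannot satisfy it. The quarter coding is compatible with a landmark, but the text does not impose one. An analyst who follows the Machine Learning section literally would build the biased data set, and the screen would then favour drugs in a known direction rather than by chance.

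**Working it through.** **1. Reproduce Table 1 (active-3, medium dose).** Lift = confidence / base survival, so base = 0.5000/6.4054 = 0.0781. Conviction = (1 − base)/(1 − confidence), so base = 1 − 1.8438 × 0.5 = 0.0781. The two agree. The lift of 6.4 therefore compares 50% with 7.8% surviving 5 years. It is a ratio of proportions, not of survival times.

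**2. Assumptions, none of them in the documents.** The drug is inert and its start is unrelated to survival. Hazard is constant: h = −ln(0.0781)/60 = 0.0425 per month. Start rate r is 0.005, 0.02 or 0.05 per month after diagnosis.

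**3. Quarter rules.** For use at mid-quarter t, the chance of reaching 60 months is S(60)/S(t), so null lift = 1/S(t) = exp(0.0425 t).

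| Quarter | t (months) | S(t) | Null lift |
|---|---|---|---|
| 4 | 10.5 | 0.640 | 1.6 |
| 8 | 22.5 | 0.384 | 2.6 |
| 12 | 34.5 | 0.231 | 4.3 |
| 16 | 46.5 | 0.139 | 7.2 |

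**4. Any use over survival time.** Among survivors, P(use) = 1 − exp(−60r). Overall, P(use) = r/(r+h) × [1 − exp(−60(r+h))]. Lift is the ratio of the two.

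| r per month | Survivors | All | Null lift |
|---|---|---|---|
| 0.005 | 0.259 | 0.0992 | 2.6 |
| 0.02 | 0.699 | 0.312 | 2.2 |
| 0.05 | 0.950 | 0.538 | 1.8 |

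A wider set of runs used base survival of 5 to 18.1%, constant or falling hazard, and start rates of 0.05 to 0.5 per year. It gave 1.6 to 4.1.

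**5. Dose thirds.** These were simulated with the same h and r and a lognormal dose (log-scale SD 0.5 to 1.0).

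| Use pattern | Low | Medium | High |
|---|---|---|---|
| One 3-month course | 3.2–5.1 | 1.2–2.6 | 0.1–1.1 |
| Continuous after start | 1.2–2.6 | 1.9–2.6 | 2.1–2.7 |

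With continuous use, lift rises from low to high in every setting (for example 1.9, 2.3 and 2.5 at 2% per month with SD 0.5). A drug in steady use from diagnosis has lift 1.0 in all three thirds.

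**6. With a 3-month landmark.** S(3) = exp(−0.1275) = 0.880, so 5-year survival among those alive at month 3 is 0.0781/0.880 = 0.0887. Users by month 3 have the same survival, so any-use lift is 1.0 (simulated 0.996 to 1.007). The wider set of runs gave 0.93 to 1.07.

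**The case against.** **The bias section may already cover this.** It speaks of the analyses in general, and the Discussion repeats that the time frame is shortened for each patient. That may be the intention. The quarter coding could be read with a landmark, but the dose definition cannot, and nothing says which text governs.

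**The rules are an additional step.** The protocol says so, and adds that the rules will be confirmed by classical analyses. The Statistical Analysis section compares survival for every drug in the database, whatever the rules return. This stands. A reader might infer that the artefact decides which drugs go forward, but the documents do not support that. Lift is also only an example among four metrics, and the support threshold may be filtered again later.

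**Table 1.** A reader might set the quarter-16 null lift of 7.2 beside the table's 6.4 and conclude that the leading example is an artefact. The two are not comparable: the 6.4 belongs to a medium-dose rule, whose null lift in step 5 is at most about 2.6. The table is also presented only as an example.

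**The sizes depend on assumptions.** This stands. The dose pattern reverses between one-off and continuous use, and drugs in steady use at diagnosis are unaffected.

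**Drugs prescribed in the 3 months before death are dropped.** This does not help without a landmark, because it removes exposure only from those who die. At r = 0.02, overall P(use) falls from 0.312 to 0.275, and null lift rises from 2.2 to 0.699/0.275 = 2.5.

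**Conclusion.** The concern holds in a limited form. The exposure definitions for the association rules conflict with the protocol's own landmark safeguard. Followed literally, they inflate lift for inert drugs started after diagnosis. With constant hazard, base survival of 7.8% and start rates of 0.5 to 5% per month, null any-use lift is about 1.8 to 2.6 instead of 1.0. Quarter-rule lift rises steadily with the quarter. Dose-third lifts are distorted in a direction that depends on how the drug is used.

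The damage is confined to the machine-learning screen and its ranking by metrics such as lift. Exploratory status covers chance findings; it does not excuse a systematic bias that the protocol itself names. Reading a lift of 6.4 as longer survival is a separate, minor wording error: the section defines lift correctly elsewhere. Overall this should be fixed, but it does not invalidate the study.

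**What to change.** State in the Machine Learning section that the landmark rule governs both rule sets:

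- Include only patients alive at landmark L.
- Use as antecedents the drugs, and the mean dose, dispensed in a fixed window up to L, with the same denominator for everyone.
- Compute lift against 5-year survival among all patients alive at L.
- Repeat at successive landmarks.

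Keep patients who start the drug after L in that base. The bias section also removes later starters and compares with never-users. That is a separate question, and the lift of 1.0 in step 6 does not rest on it.

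Correct the Table 1 sentence to say that the proportion surviving 5 years is about 6 times the expected proportion. Ranking by the lower confidence limit of lift is optional.

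The cost is re-preprocessing data already held, re-running any rules already generated, and two wording changes. The downside is that drugs used only late are assessed only at later landmarks.

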## Introduction

The usefulness of new cancer treatments is traditionally analyzed in clinical trials, which are considered the most rigorous design to study the effects of a treatment on a disease. Despite their strengths, clinical trials have significant limitations, such as cost and time. In a typical clinical trial, one or very few treatments are tested over a course of 7.5 years, and in oncology, the costs range from US $4.5 million (phase I) to US $22.1 million (phase III) [1-4]. Despite this, the clinical trials database ClinicalTrials.gov registers more than 22,000 trials each year, accounting for billions spent annually on clinical trials [5].

In oncology, the results of this substantial financial investment are modest, at best. As an example, only 5% of the molecules tested in phase 1 trials are marketed, and even if they are, they rarely generate a substantial change in the prognosis of patients [6,7]. In addition, the issue seems to be getting worse because the number of approved molecules has not increased in recent decades, but investment by the pharmaceutical industry has increased significantly [8].

Various strategies have been used to try to improve the efficiency of clinical trials. One of the most interesting is drug reuse (drug repurposing), with the aim of finding new uses for existing drugs approved for another therapeutic indication. This approach can, in most cases, allow research to begin with phase 2 trials because preclinical, pharmacokinetic, pharmacodynamic, and toxicity data are usually already known [7]. Looking for new treatments among already known molecules does not seem unreasonable, because in Spain alone, there are more than 2600 active ingredients approved and in use; it makes sense to think that some of them may have unknown effects on cancer. This approach, however, faces significant challenges since the complex and heterogeneous nature of cancer means that drugs with an effect on one type of cancer may not exhibit similar efficacy in several subtypes of cancer. Additionally, issues related to intellectual property, regulatory pathways, and the need for robust clinical evidence contribute to the complexity of drug repurposing efforts in oncology [9,10].

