**Combination of active ingredients**												
	active-3 and active-2	Medium, low		Survival	0.0021		7	0.8888		11.3873		8.2974
	active-5 and active-1	Low, low		Survival	0.0015		6	0.7500		9.6081		3.6877
	active-4 and active-2	High, low		Survival	0.0013		5	0.7142		9.1505		3.2267

In addition, it is possible to filter by age, gender, or patient group, as well as search for relationships between them and their survival. Similarly, combinations of active ingredients can be sought that lead to increased survival (Table 1).

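### Association rules need only 5 patients and are ordered by metrics that ignore the number of users, so chance rules in small groups can crowd the top of the list

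*Protocol article*

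**What the plan says.** All statements are in the protocol article, Methods, Machine Learning, unless noted.

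- **Floor.** Of the rules generated, "only those that are met in at least 5 patients will be taken into consideration". The patients counted are those with both the antecedent and survival. The number is later given as an example of a support threshold, followed by "However, this support can be filtered again later". No later value is fixed.
- **Ordering.** "Finally, the filtered rules are sorted by the desired metric (eg, lift". The reason given for lift is: "This metric was chosen especially for its ability to find active ingredients with a higher-than-expected survival rate". Support, confidence and conviction are the other listed metrics. None comes with an interval, a P value or shrinkage.
- **Breadth.** The Introduction says that in Spain "there are more than 2600 active ingredients approved and in use". For the dose-based rules, "the average DDD, discretized in 3 quantiles, will be used during the survival time of the patient". The text around Table 1 adds that "combinations of active ingredients can be sought that lead to increased survival".
- **What follows.** "The associations identified by machine learning techniques will later be confirmed by the classical statistical analyses described below". The Statistical Analysis section tests each drug and each drug family at P=.05 without correction. The Discussion says that a false discovery rate adjustment will be considered.

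**The concern.** Lift is an observed ratio. A group of 12 users can reach a lift above 5 with 5 survivors, whereas a group of several hundred can do so only if the effect is enormous. When thousands of items are screened, the extremes of an unweighted ratio come mostly from the smallest groups. A list ordered this way tends to put imprecise results first and to push a moderate, well-estimated effect in a common drug down the page.

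The purpose of the step is to point to drugs and combinations worth following up. If its order does not reflect strength of evidence, follow-up effort goes to the wrong candidates.

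**Working it through.** **1. Do the other listed metrics help?** Write c for confidence and b for the proportion alive at 5 years in the data set. The consequent is fixed, so b is constant.

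- lift = c / b
- conviction = (1 − b) / (1 − c)

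Both rise with c alone, so confidence, lift and conviction give one and the same order. Support is survivors with the antecedent divided by all patients. It is a count, and it favours common drugs whether or not they have an effect. None of the four measures precision.

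**2. Reproducing Table 1.** b = 0.5000 / 6.4054 = 0.0781. Users = n / c, for example 30 / 0.5000 = 60 and 5 / 0.4166 = 12. Conviction for active-3 is (1 − 0.0781) / (1 − 0.5000) = 1.844, as printed. Total patients are 30 / 0.0079, about 3,800.

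For active-2, and for active-3 with active-2, the printed n of 7 does not fit the support: 0.0021 × 3,800 = 8.0. The printed confidences fit 8/20 and 8/9, so both readings are shown.

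**3. Exact (Clopper-Pearson) 95% limits, divided by b.** The last column is the binomial probability of at least that many survivors at rate b.

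| Rule | Survivors/users | Lift | 95% limits for lift | Chance probability |
|---|---|---|---|---|
| active-3 | 30/60 | 6.4 | 4.7 to 8.1 | 7e-18 |
| active-5 | 31/71 | 5.6 | 4.1 to 7.2 | 3e-16 |
| active-1, active-4 | 5/12 each | 5.3 | 1.9 to 9.3 | 0.0014 |
| active-2 | 8/20 (7/18) | 5.1 | 2.4 to 8.2 (2.2 to 8.2) | 7e-5 (3e-4) |
| active-3 and active-2 | 8/9 (7/8) | 11.4 | 6.6 to 12.8 (6.1 to 12.8) | 1e-8 (1e-7) |
| active-5 and active-1 | 6/8 | 9.6 | 4.5 to 12.4 | 6e-6 |
| active-4 and active-2 | 5/7 | 9.2 | 3.7 to 12.3 | 5e-5 |

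Sorted by lower limit within each block, active-2 moves above the two 5-of-12 rules. The top two single drugs and the order of the pairs stay as they are.

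**4. Where high chance lifts come from.** At b = 0.0781, the chance of a lift of 3 or more (with at least 5 survivors) is 0.009 for 24 users, 6e-7 for 100 users and 7e-12 for 200 users. If 2,600 inert drugs each had 12 users, 2,600 × 0.00144 = 3.7 would reach 5 survivors by chance. With three dose levels of 12 users each the figure is 11.

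**5. Effect on the ranking (simulation, assumed inputs).** The article does not give the number of items or the users per item. I assumed inert items at 7.8% survival with log-uniform users, plus 10 true items with 300 users each at 14.1% (a ratio of 1.8) and a floor of 5 survivors. The outcome is the number of true items among the first 20.

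| Inert items | Users per inert item | By lift | By lower 95% limit |
|---|---|---|---|
| 1,500 | 12 to 800 | 2.0 | 8.6 |
| 500 | 12 to 800 | 6.5 | 9.6 |
| 1,500 | 12 to 3,000 | 2.9 | 8.8 |
| 1,500 | 50 to 800 | 4.8 | 8.6 |

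In the first row the median group size in the lift top 20 is 37. A repeat run agreed within 0.2 in every cell of the last two columns.

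**6. At the protocol's own effect ratio.** Sample Size Considerations uses 20% against 30%, a ratio of 1.5; its 294 per group reproduces (two-sided 5%, power 80.1%). With 500 to 2,600 inert drugs, 1 or 3 dose levels and an assumed 5 to 1,500 users per drug, a true lift of 1.5 in 600 users has a median rank of 20 to 298 by lift and 1 to 3 by exact P value.

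**The case against.** Several points on the other side are sound.

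- **Table 1 does not show a list full of noise.** A reader might compare the 6-of-8 and 5-of-7 pairs with the 30-of-60 single drug and infer that it does. The article lists pairs and single drugs in separate blocks and never ranks across them. Among single drugs the two largest groups come first, far beyond chance. The 8-of-9 pair stays first by lower limit as well. Over an assumed 3,300 pairs of the relevant size, chance would give about 0.18 rules like 5 of 7 and 0.02 like 6 of 8. The true number of eligible pairs is unknown.
- **Real effects in common drugs are not lost.** A reader might infer that they are. Rule mining is an additional step, and the Statistical Analysis section compares survival for every drug and family regardless of its rank.
- **The ranking is not stated to be the main route for pairs.** The same section plans analyses of two or more drugs found to influence survival.
- **The procedure is loosely fixed.** Lift is an example, support may be refiltered, and no rank cut-off is stated, so the top 20 above is only illustrative.

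These points limit the harm but do not remove the fault. Replacing lift by confidence or conviction changes nothing in the order. Refiltering has no stated value. The confirmation names no separate data, so a chance rule retested in the same patients tends to pass at an uncorrected P=.05. The control cohort removes only findings that recur there, and a chance finding in the cancer cohort usually would not.

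**Conclusion.** The concern holds in a limited form. A 5-patient floor, combined with an ordering that ignores the number of users, lets chance rules in small groups dominate the top of the list and places moderate effects in common drugs below them. Under the assumed inputs, lift brings 2 to 6.5 of 10 true items into the first 20, against 8.6 to 9.6 for the lower limit. The direction is the same in all four settings. The size rests on the assumed item counts, user distribution, effect and cut-off, none of which the article states.

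The documents do not support saying that the list is in fact filled with chance results: that depends on those unstated numbers, and in Table 1 only the last three single-drug rows change places. The consequence is a less efficient screen, chiefly for combinations and small user groups. The check concerns sampling error only and says nothing about bias in the rules.

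**What to change.** In the Machine Learning section, replace lift as the sort key by the exact binomial lower 95% limit of confidence (or of lift, which gives the same order), applied separately within single drugs and within combinations. In tables such as Table 1, print the number of users and the 95% interval for every rule.

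The cost is one computed column and a changed sort key, with no new data. The downside is that rules in very small groups will be carried forward less often. Raising the floor also helps: with 1,000 drugs at three dose levels, a floor of 30 instead of 5 moves the median rank by lift of a true lift of 1.5 in 600 users from 125 to 4. However, it discards small groups outright, so the lower limit is preferable.

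False discovery control across all rules is a separate multiplicity question and is not needed for this change.
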